#### 2.2.4. Data Management

All data will be stored on a password-protected computer and a central hard disk of the research group. The data of the participants will be pseudonymized, and only the main researcher will have access to the key to link raw data on personal data. Data will be stored for a minimum of 5 years after the appearance of publications based on these data. After this period, the data can be destroyed.

#### 2.2.5. Ethics Approval and Consent to Participate

This study and its three parts (co-creation, pilot study, and RCT) have been submitted for approval by the Committee of Medical Ethics of the Ghent University Hospital. Ethical approval has already been received so as to coincide with the beginning of the co-creation sessions (EC number: BC-11748). The RCT will be registered at ClinicalTrials.gov, which is a database of privately and publicly funded clinical studies conducted around the world. Participants in the co-creation sessions, the pilot study, and the RCT will receive an information letter and informed consent to provide them with all of the details about the study. Grandparents and parents will be asked to read and sign the informed consent; grandchildren will be asked to sign an informed assent before the start of the co-creation sessions, pilot study, and RCT. Each participant will be informed about the purpose of the study, the design, the procedure, the right to leave the study at any time, and the data confidentiality.

## 3. Research Intention

The research intention of the program development and evaluation is a theory-based lifestyle program which aims to improve Physical Activity and Cognitive functioning in GRANDchildren and their GRANDparents using co-creaTion (i.e., the GRANDPACT Project).

For the program development, it is expected that a theoretical framework, in combination with a co-creation approach, will lead to an attractive and feasible intergenerational movement program in which grandchildren can participate together with their grandparents. The needs and requirements of end-users will be taken into account, and this will make them feel empowered. For the program’s evaluation, it is expected that the pilot study will help to refine the movement program that will be drafted after the co-creation sessions. Furthermore, the refinement of measurement instruments, recruitment strategies, ages, and group sizes will be important to optimize the program for the RCT. The RCT will be conducted to evaluate effects of the (cognitively enriched) intergenerational movement program on co-PA, cognitive functioning, psychosocial well-being, and quality of the family relationship.

Arm 1 of the RCT will mainly focus on increasing co-PA (i.e., PA between grandchild and grandparent), while Arm 2 of the RCT will mainly focus on increasing cognitive functioning in both the grandchildren and grandparents via a *cognitive enrichment* of co-PA (i.e., cognitively enriched PA between grandchild and grandparent). The main goal and primary outcome of the intervention is to improve co-PA in grandchildren and grandparents (based on the WHO PA guidelines), and taking feasibility into account, we aim to reach a level where grandchildren are physically active together with their grandparents 2 times per week, for a minimum of 30 min of performing MVPA. The secondary goal is to improve total PA, cognitive functioning, psychosocial well-being, and quality of the family relationship in grandchildren and their grandparents, and it is expected that co-PA (over a period of 36 weeks) will act as a mediator in this relationship. It is hypothesized that Arm 1 (focusing on intergenerational PA) and Arm 2 of the RCT (focusing on intergenerational cognitively enriched PA) will lead to a greater improvement in PA, cognitive functioning, psychosocial well-being, and quality of the family relationship than that of the control group (no intervention). Furthermore, it is expected that the cognitive enrichment of the intergenerational movement program will lead to a greater improvement in cognitive functioning in Arm 2 of the RCT.

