Health behaviour is, in general, influenced by the combination of three broad categories of determinants: capability, opportunity, and motivation (COM-B). In the co-creation sessions, the researchers will investigate why people show or do not show a specific behavior based on these three types of determinants (e.g., for the health behaviour of PA, are grandchildren and grandparents able to be physically active together; do they have opportunities to be physically active together; and are they motivated to be physically active together?). The sources of behaviour will be taken into account (physical, social, psychological, reflective and automatic), but other sources of behavior will also be considered (e.g., technological), which could result in an extended version of the BCW, including new determinants. 

Furthermore, the threats, barriers, and difficulties to setting the PA behavior will be investigated using the Theoretical Domains Framework (TDF). These TDFs are subcategories of the three broad categories. Examples of TDFs are given in Figure 3 [47]. 

The primary outcomes will be PA and cognitive functioning in both grandchildren and grandparents; the secondary outcomes will be psychosocial well-being and the quality of the family relationship between grandchildren and grandparents. We expect to see improved levels of PA, cognitive functioning, psychosocial well-being, and quality of the family relationship in the intervention group. Cognitive functioning will improve more in grandchildren and grandparents who participate in the cognitively enriched intergenerational movement program. 

Step 5: Intervention functions

The project researchers will consider the cases that emerged from Step 4 and will determine which intervention function is best suited to change the behaviour (i.e., a lack of PA). Intervention goals will also be drafted, which will then be presented to the grandchildren and grandparents in the co-creation sessions, where they can give their input and feedback. 

Step 6: Policy categories

In this step, policy categories will be identified. The policy categories will need to support the intervention functions in Step 5. It will be of great value that the sessions will be embedded in an organization afterwards so as to ensure sustainable implementation. Some examples of organizations and policy categories are Family Sport Flanders, senior and youth sports, and municipal sports.

Step 7: Behaviour change techniques

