## 4. Discussion of the Research Intention

This paper describes the study protocol of the GRANDPACT Project. The main aim of this project is to develop an effective, attractive, and feasible (cognitively enriched) intergenerational movement program for grandchildren and their grandparents to improve their co-PA and cognitive functioning (primary outcomes), psychosocial well-being, and the quality of the family relationship between the grandchildren and their grandparents (secondary outcomes).

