### 4.3. Implementation of This Intervention

Implementation of the intervention program is likely to impact its success; therefore, several strategies will be used to facilitate correct implementation of the intergenerational movement program by different organizations (e.g., Family Sports Flanders and Sports Flanders). First, a detailed protocol will be written to assure that the intervention will stay theory-based and to minimize attrition rates, which will both foster the success of the intervention (i.e., this protocol will be the common thread; researchers, stakeholders, grandchildren, and grandparents should respect this protocol). Second, the expert meetings with diverse stakeholders from different organizations (e.g., GRAY, Family Sports Flanders, and MOEV) that will be held after the co-creation trajectories will help to gain feedback and additional advice about the feasibility of implementing the cognitively enriched movement activities for grandchildren and grandparents (e.g., body posture, execution of movements, and other aspects that require attention). This input will also be integrated into the protocol. Third, the planned pilot study will help to refine the cognitively enriched movement activities to ensure that they will be useful and correctly executed, as well as attractive and feasible for the target population. If results of the RCT show that the intervention is indeed effective at improving co-PA and cognitive functioning in the first place, and psychosocial well-being and the quality of the family relationship in the second place, a meeting with organizations who are interested in implementing this intergenerational movement program will be held to discuss the information necessary for grandparents, parents, and children, which materials are needed, which locations are preferable and feasible, which certified teachers should be recruited, etc. A very important factor is that the embedding of this project in GRAY will help to engage Flemish partners, such as Family Sports Flanders and Sports Flanders, in its execution, dissemination, and valorization.

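### The protocol gives three incompatible sets of primary outcomes, and the sample-size paragraph is tied to none of them

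*Protocol article*

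**What the plan says.** The protocol article ranks the RCT outcomes in three places.

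- Section 2.1.1, Step 4 of the Behaviour Change Wheel: "The primary outcomes will be PA and cognitive functioning in both grandchildren and grandparents". Well-being and family relationship are secondary there, and co-PA is in neither list.
- Section 3, Research Intention: "The main goal and primary outcome of the intervention is to improve co-PA in grandchildren and grandparents". The same paragraph continues: "The secondary goal is to improve total PA, cognitive functioning, psychosocial well-being, and quality of the family relationship".
- Section 4, Discussion of the Research Intention, describes a program "to improve their co-PA and cognitive functioning (primary outcomes), psychosocial well-being" and the family relationship, the last two being secondary. Total PA is in neither list.

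Section 4.3 uses the Section 4 pair as the condition for meeting implementing organizations. That meeting follows if the RCT shows the program to be "effective at improving co-PA and cognitive functioning in the first place".

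The sample-size paragraph in Section 2.2.3 gives an effect size of 0.15, 80% power, alpha 0.05, three groups and three measurements. It arrives at about 45 dyads (90 individuals), raised to 54 dyads (108 individuals) for attrition. It applies these figures to PA, cognitive functioning, well-being and family relationship alike, ranks none of them first and does not list co-PA.

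**The concern.** The primary outcome decides whether the trial succeeded, and the alpha and sample size are meant to protect that decision. Here three sections give three answers. A later report could present PA, co-PA or cognitive functioning as the pre-specified primary and cite a published section in support. Section 4.2 acknowledges that there is no blinding and that the researcher takes part in both data collection and analysis, so firm pre-specification matters more than usual.

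Arm 2 is affected most. Section 3 says that this arm mainly targets cognitive functioning, yet ranks cognitive functioning as secondary in the same paragraph. Whether its central hypothesis is confirmatory depends on the section read.

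An analysis plan cannot settle this alone. It could implement only one of the three statements and would then contradict the other two.

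**Working it through.** **Step 1. The statements side by side**

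| Place | co-PA | Total PA | Cognitive functioning |
|---|---|---|---|
| 2.1.1, Step 4 | not listed | primary (as PA) | primary |
| 3 | primary | secondary | secondary |
| 4 (and 4.3) | primary | not listed | primary |
| 2.2.3, sample size | not listed | powered (as PA) | powered |

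No outcome holds the same rank in Sections 2.1.1, 3 and 4. If PA in Step 4 is read as co-PA, the first and third rows agree, but cognitive functioning is still primary in both and secondary in Section 3.

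**Step 2. Reproducing the planned sample size**

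Inputs from Section 2.2.3: effect size 0.15, g = 3 groups, m = 3 measurements, alpha 0.05, power 80%. Assumptions not in the document: the effect size is Cohen's f, the test is the group-by-time interaction of a repeated-measures ANOVA, the correlation between repeated measures is ρ = 0.5, and sphericity holds.

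- λ = f²·N·m/(1−ρ) = 0.0225 × 90 × 3 / 0.5 = 12.15
- df1 = (g−1)(m−1) = 4; df2 = (N−g)(m−1) = 87 × 2 = 174
- Power at N = 90 is 79.6%. The smallest N for 80% is 91 (93 in equal groups).

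The stated figure of around 90 therefore reproduces as one test at 0.05 on 90 individuals treated as independent. That matches a single individual-level primary outcome.

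**Step 3. What each version implies at the planned size (ρ = 0.5)**

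- *One individual-level primary at 0.05:* 79.6% power.
- *Two primaries, both required:* each is tested at 0.05 and no split is needed. The chance of winning on both is 0.796² = 63% if the two tests are independent, and higher if they are positively correlated.
- *Two primaries, either sufficient, no split:* familywise error is 1 − 0.95² = 9.75% for independent tests.
- *Two primaries, either sufficient, 0.025 each:* power per outcome at N = 90 is 70.6%. Reaching 80% needs 108 evaluable individuals in equal groups, or 108/0.8 = 135 recruited at 20% attrition.
- *co-PA as one value per dyad at 0.05:* N = 45 units, λ = 0.0225 × 45 × 3 / 0.5 = 6.075, df2 = 84, power 45.2%.

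**Step 4. Sensitivity to the assumed correlation**

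| Case | ρ = 0.3 | ρ = 0.5 | ρ = 0.7 |
|---|---|---|---|
| N = 90, alpha 0.05 | 63.2% | 79.6% | 96.1% |
| N = 90, alpha 0.025 | 52.0% | 70.6% | 93.1% |
| N = 45, alpha 0.05 | 32.8% | 45.2% | 69.4% |

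Only ρ near 0.5 reproduces the stated sample size. The ordering of the three cases is the same throughout.

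**The case against.** The strongest reply is that the conflict is smaller than it looks. The article uses PA and co-PA loosely: the abstract lists co-PA as an outcome and then gives accelerometry as the measure of PA, and Step 2 of the Behaviour Change Wheel section makes co-PA the target behaviour through which overall PA should improve. On that reading Step 4, Section 4 and Section 4.3 agree, and Section 3 is the outlier. This has some force, but it does not remove the problem. Section 3 separates total PA from co-PA, the first item of the TIDieR checklist lists both, and the rank of cognitive functioning conflicts on any reading.

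A second reply is that the RCT is still to be registered and the pilot will settle the instruments, so the choice can yet be fixed. That is true, and it is why correction is cheap now. The article does not say which of its statements the registration will carry.

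A reader might also go further and count three arm pairs, two generations and two outcomes as separate tests at 0.05. Treated as independent, 3, 9 or 12 tests give error rates of 14%, 37% or 46%, which would suggest that the error rate differs several-fold between versions. The documents do not support this. They give 0.05 for the sample-size calculation and do not say that every pairwise contrast is tested at that level, that generations are analysed separately for confirmation, or that any single positive result counts as success. Three arm pairs share arms, so even unadjusted the rate is about 12.2%, not 14%. Section 4.3 can be read as requiring both outcomes, which would not inflate the error across outcomes. Multiplicity handling may properly sit in an analysis plan that is not shown. What follows from the contradiction itself is one primary against two: 5% against at most 9.75%.

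**Conclusion.** The point stands as an internal contradiction. The protocol gives three sets of primary outcomes that cannot all hold, and a sample-size paragraph that matches none of them. Following the document as written leaves the deciding outcome open. This should be corrected before the RCT is registered.

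Its size depends on the version chosen. At the planned 90 individuals, power is about 80% for one individual-level primary, about 71% for each of two at 0.025, and about 45% for a single co-PA value per dyad. The familywise error is 5%, or at most 9.75% if two primaries are tested unsplit with either sufficient. The power figures assume Cohen's f = 0.15, ρ = 0.5 and a group-by-time interaction test; at 90 units they also treat grandchild and grandparent as independent. The 9.75% assumes independent tests and a success rule that the document neither states nor excludes.

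A reader might infer that co-PA must become the sole primary because Section 3 says so most directly. The documents do not compel that. Section 2.2.3 leaves the feasibility of Bluetooth measurement of co-PA to be assessed, describes the diary as a way to study context, and does not list co-PA among the powered outcomes.

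**What to change.** Before registration, choose one primary-outcome statement and use it in Step 4 of Section 2.1.1 and in Sections 3, 4 and 4.3. Distinguish total PA from co-PA by name wherever either is meant.

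State the success rule with it:

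- one primary outcome at 0.05;
- two primaries, both required, each at 0.05; or
- two primaries, either sufficient, with alpha split between them.

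Then tie the sample-size paragraph in Section 2.2.3 to that choice. Name the outcome and the unit of analysis (individual or dyad), state the effect-size metric and the assumed correlation, and restate the power. Say whether Arm 2's cognitive hypothesis is confirmatory.

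Making co-PA the sole primary is one option. It would need a settled measurement method and, if there is one value per dyad, a new sample-size calculation.

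The cost is protocol wording, a restated and possibly less favourable power figure (or a larger sample), and fewer outcomes that can carry a confirmatory claim.

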## 4. Discussion of the Research Intention

This paper describes the study protocol of the GRANDPACT Project. The main aim of this project is to develop an effective, attractive, and feasible (cognitively enriched) intergenerational movement program for grandchildren and their grandparents to improve their co-PA and cognitive functioning (primary outcomes), psychosocial well-being, and the quality of the family relationship between the grandchildren and their grandparents (secondary outcomes).

### 4.1. Importance of This Study

The development of this intergenerational movement program for grandchildren and grandparents is innovative for the following four reasons. First, to our knowledge, this will be the first intervention that uses the Behaviour Change Wheel in combination with a co-creation approach to develop a cognitively enriched intergenerational movement program for grandchildren and grandparents. Previous intergenerational interventions described in literature are often not evidence-based or grounded by a theoretical framework, and if so, mostly the Social Cognitive Theory was used for the development of the PA intervention [42,43]. However, this behaviour change model has some shortcomings, which are covered by the Behaviour Change Wheel [37]. The Run Daddy Run intervention used the Behaviour Change Wheel in combination with a co-creation approach to develop an intervention targeting PA in fathers and children (co-PA) to improve children’s lifestyle behaviours. This combination seemed to be effective in developing this intervention and reaching the expected goal [76]. Therefore, and also because this study focuses on family members, this method has been chosen for this study. Second, to our knowledge, grandchildren and grandparents who do not live together have never been involved in the development of an intergenerational movement program. In the literature, only one program focused on intergenerational PA, but in the context of kinship families, where grandparents are raising their grandchildren and living with them [36]. However, this situation is not a ‘standard situation’ in Belgium, nor is it common in other, large parts of the world where most grandchildren live apart from their grandparents. The main finding of this study, which focused on grandparents raising their grandchildren, is that the community-based participatory research (CBPR) framework seems to be an effective approach to improving health outcomes and to implementing the intervention, which reaffirms the value of the co-creative approach in developing health promotion interventions. Furthermore, it is expected that intrafamilial relations may strengthen the motivation to be physically active together and to make a long-term commitment. Thirdly, the quality of the family relationship between grandchildren and grandparents, which will be investigated in this study, has already been explored [74,75], but not in a context in which they engage in organized activities together. It can provide an interesting insight into how the relationship between them changes from the way it was before they performed the movement activities together. Lastly, the combination of PA and cognitively enriched activities has never been used in intergenerational research. The focus in intergenerational programs mainly consists of doing organized activities together. Most of the time, these are creative, physically active, or cognitively stimulating activities that children and older adults perform together [65]. Both PA intergenerational programs and intergenerational programs focusing on cognitive functioning alone do exist, but none of these programs uses the combination of PA and cognitive functioning in the same program, while there is evidence that the combination of PA and cognitively enriched tasks results in even better cognitive functioning [17,21]. Therefore, the use of this combination can lead to a greater improvement in the cognitive functioning of both the grandchildren and the grandparents.

### 4.2. Potential Strengths and Limitations of This Study

A first potential strength of this study includes the experimental and longitudinal design. A second potential strength is the use of the Behaviour Change Wheel in combination with a co-creation approach in which end-users and stakeholders will collaborate in the development of the movement program. This may lead to a more effective intervention, and it will also prevent drop-out because the needs and preferences of the grandchildren and grandparents will be taken into account [51,52,53,54]. In addition, organizations working with children and older adults (stakeholders) will be asked to offer information about the usefulness, attractiveness, and feasibility of the movement activities (i.e., a bottom-up instead of a top-down approach, which means that researchers base the research upon the end-users, rather than upon a general theory or idea based on findings in the literature) [77]. A last potential strength is that PA and cognitive functioning will be measured objectively through accelerometry and CANTAB tests, while self-report measures (e.g., questionnaires and diaries) can lead to response and recall biases [78].

A first potential limitation of this study includes the lack of blinding, as the researcher will be involved in the data collection and analysis. Therefore, a strict protocol has been created so as to reduce this limitation as much as possible. A second potential limitation includes the recruitment strategy. Convenience sampling will be used for the co-creation sessions, the pilot study, and the RCT. It is therefore expected that grandchildren and grandparents who are already more physically active and motivated to move will be interested participating. However, this will be taken into account during the recruitment by mentioning that the levels will be attainable for everyone and that the focus will not only be on the movement activities, but also on creating a pleasant atmosphere by making the activities fun, attractive, and feasible for the target group.

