#### 2.2.3. Randomized Controlled Trial (RCT)

The RCT will be conducted subsequent to the pilot study so as to measure the effects of the two different programs on the outcomes of PA, cognitive functioning, psychosocial well-being, and quality of the family relationship in the grandchildren and grandparents and to evaluate the process of the study. The RCT will consist of two intervention groups, Arm 1: Intergenerational PA and Arm 2: Cognitively enriched intergenerational PA, and one control group. Intervention Group 1 will receive the intergenerational movement program, Intervention Group 2 will receive the cognitively enriched intergenerational movement program, and the control group will receive no intervention. The pre- (before the start of the sessions), post- (after 24 weeks) and follow-up (after 36 weeks) outcome measures of PA, cognitive functioning, psychosocial well-being, and quality of the family relationship will be compared between Group 1 and the control group, between Group 2 and the control group, and between Groups 1 and 2. An overview of the RCT is shown in Figure 5.

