	**HOW WELL**		
11.	To assess intervention adherence and fidelity, a protocol study has been written out to think about different aspects (participants, sample size, measurement instruments) in order to reduce bias. Furthermore, providers of the intervention will have received a training or will be experts in what they have to perform. The measurement instruments that will be used during the intervention are all validated and reliable for children and older adults.	pp. 13, 16–17	_____________
12. ^ǂ^	Actual: If intervention adherence or fidelity was assessed, describe the extent to which the intervention was delivered as planned. This will be described when the RCT has ended.		_____________

** **Authors**—use N/A if an item is not applicable for the intervention being described. **Reviewers**—use ‘?’ if information about the element is not reported/not sufficiently reported. † If the information is not provided in the primary paper, give details of where this information is available. This may include locations such as a published protocol or other published papers (provide citation details) or a website (provide the URL). ǂ If completing the TIDieR checklist for a protocol, these items are not relevant to the protocol and cannot be described until the study is complete. Note 1: We strongly recommend using this checklist in conjunction with the TIDieR guide (see *BMJ* 2014; 348: g1687) which contains an explanation and elaboration for each item. Note 2: The focus of TIDieR is on reporting details of the intervention elements (and where relevant, comparison elements) of a study. Other elements and methodological features of studies are covered by other reporting statements and checklists and have not been duplicated as part of the TIDieR checklist. When a **randomised trial** is being reported, the TIDieR checklist should be used in conjunction with the CONSORT statement (see www.consort-statement.org) as an extension of **Item 5 of the CONSORT 2010 Statement.** When a **clinical trial protocol** is being reported, the TIDieR checklist should be used in conjunction with the SPIRIT statement as an extension of **Item 11 of the SPIRIT 2013 Statement** (see www.spirit-statement.org). For alternate study designs, TIDieR can be used in conjunction with the appropriate checklist for that study design (see www.equator-network.org).

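### The only stated mitigation for unblinded data collection and analysis is a strict protocol that is not shown to mask the arm; processing and analysis could be masked at little cost

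*Protocol article*

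**What the plan says.** Section 4.2 of the protocol article names as the first limitation "the lack of blinding, as the researcher will be involved in the data collection and analysis". It follows this with one mitigation: "a strict protocol has been created so as to reduce this limitation as much as possible". The same section counts it as a strength that "PA and cognitive functioning will be measured objectively through accelerometry and CANTAB tests".

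Two other places describe what a protocol is meant to do. Table A1, item 11 (HOW WELL) says "a protocol study has been written out to think about different aspects (participants, sample size, measurement instruments) in order to reduce bias". Section 4.3 says "a detailed protocol will be written to assure that the intervention will stay theory-based and to minimize attrition rates".

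On data access, Section 2.2.4 says "The data of the participants will be pseudonymized" and that "only the main researcher will have access to the key to link raw data on personal data".

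On the comparator, Section 2.2.3 says "the control group will receive no intervention".

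**The concern.** The limitation covers two stages, collection and analysis, and the mitigation is not matched to either. A standardised procedure makes people do the same thing each time. It does not stop the person doing it from knowing the arm.

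Knowledge of the arm matters most where choices remain after measurement. In this trial the primary outcome is not settled in the text, co-physical activity may be built from more than one source, and there are two generations, three pairwise comparisons and three time points. An analyst who knows the arms can favour one route over another without intending to. That risk remains even when the instrument itself is automated. If the trial reports an effect, readers will ask whether the processing and modelling were fixed without knowledge of allocation, and on the present text the answer would be no.

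**Working it through.** The question is mainly one of reading. The only arithmetic is a standard error, given last for scale.

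1. **Is the lack of blinding a stated choice or a detail left to another document?** It is stated. Section 4.2 gives the arrangement, the reason for it and the one mitigation. A fuller protocol or an analysis plan could add procedures, but the article presents unblinded collection and analysis as the design.

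2. **Does the visible text show that the strict protocol masks the arm?**
   - Section 4.2 gives no content for it.
   - Table A1, item 11 lists participants, sample size and measurement instruments.
   - Section 4.3 gives the theory base and attrition.
   - Section 2.2.4 covers pseudonymisation, which concerns identity. It says nothing about coding the arm or about who holds the allocation list.

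   None of these mentions coded arms, an assessor unaware of allocation, or a separate analyst.

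3. **Which stages could be masked?**
   - Participants and session leaders: no, because the comparator is no intervention.
   - Data collection (CANTAB sessions, questionnaires, diary): not by coding the arms. That would need assessors who do not know the allocation.
   - Processing and analysis: yes. Data are already pseudonymised, and Section 2.1.1 refers to project researchers in the plural.

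4. **How much room for choice is visible?**
   - Primary outcome: Section 2.1.1, Step 4 gives physical activity and cognitive functioning. Section 3 gives co-physical activity, with total physical activity and cognition as secondary. Section 4 gives co-physical activity and cognitive functioning.
   - Comparisons: Section 2.2.3 plans three pairwise contrasts over three time points, in grandchildren and grandparents.
   - Models: the Data Analysis part of Section 2.2.3 plans multilevel models and a path analysis.
   - Co-physical activity: the Outcome Measures part of Section 2.2.3 has accelerometers, a diary with start and end times and rated intensity, and possibly a Bluetooth signal.

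5. **Would X/Y/Z codes stay masked?** Only with care. Session questionnaires and accelerometer records from sessions can exist only in the two intervention arms. If they sit in the analyst's file, they identify the control arm.

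6. **Scale.** Section 2.2.3 calculates 45 dyads and plans 54 after allowing for attrition.
   - 45/3 = 15 dyads per arm, so 15 people per arm within one generation; 54/3 = 18.
   - With SD = 1, the standard error of an unadjusted between-arm difference at one time point is sqrt(1/15 + 1/15) = sqrt(2/15) = 0.365, or about 0.37 SD.

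   This shows that the estimates are imprecise. It says nothing about how far unmasked choices would move them.

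**The case against.** The strongest reply is that the article discloses the limitation itself, and that valid-day rules, diary matching and model specification normally sit in a fuller document. Both points are fair. The absence of those rules here is not the complaint. What stands is narrower: the article states the unblinded arrangement and answers it with a measure that is not shown to address it.

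Four stronger readings are tempting, and the documents do not support them.

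- **That the key-holder is the unblinded analyst.** Section 4.2 speaks of the researcher and Section 2.2.4 of the main researcher. Nowhere are they said to be one person.
- **That the key reveals allocation.** It links raw data to personal data. Giving such a key to one person is ordinary data protection, and it becomes a masking problem only if that person also analyses.
- **That coded arms would resolve the limitation.** They do nothing for collection, and they work less well if the analyst collected the data and can recognise dyads.
- **That a few reclassified records would shift the result by a known amount.** The documents give no basis for such a figure.

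It is also fair that the pilot study is to make the final choice of CANTAB tests before any trial data exist, which removes part of the choice over cognitive outcomes. Lastly, the claim of objective measurement in Section 4.2 is drawn against self-report. It makes no promise about later processing and is not wrong on its own terms.

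**Conclusion.** The point holds in a limited form. The article states that collection and analysis are unblinded, and its only mitigation is not shown to mask the arm at any stage. Blinding of participants and session leaders is out of reach, and masking at collection would need separate assessors. Masking of processing and analysis is feasible with what the team already has, and it is worth doing because the primary outcome differs between Sections 2.1.1, 3 and 4.

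The size of the bias cannot be quantified from the documents. The 0.37 SD above is a standard error under assumptions of 15 people per arm, unit SD and no adjustment for baseline or repeated measures. It is not an estimate of bias. Influence at collection is likely to be smaller for accelerometry and the automated CANTAB than for questionnaires and the diary.

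The conclusion rests on the visible text. If the strict protocol does contain masking steps, the article should say so.

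**What to change.** State in the protocol who is masked, at which stage and how. For processing and analysis:

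1. Have an existing team member who does not analyse the data hold both the allocation list and the identity key. If the main researcher will not analyse, the present custody of the identity key can stay, with the allocation list placed alongside it.
2. Release pseudonymised outcome data with arms coded X/Y/Z, leaving out session-only records.
3. Lock the accelerometer, diary and CANTAB processing rules and the multilevel model code, and run the primary models, before the codes are opened. This requires the primary outcome to be reconciled across sections first.
4. Where the existing team allows, choose an analyst who did not collect data. Otherwise report the masking as partial.

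In Section 4.2, replace the reference to a strict protocol with this description, and say plainly that data collection remains unblinded unless assessors unaware of the arm are used.

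The cost is a change of custody within the team and a data-lock step. Sample size, visits and intervention are unchanged. Masked assessors would reduce bias at collection too, but might need additional staff, so they are not part of this minimum change.
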